Ethiopia is an ideal setting for our proposed work, as it faces important tradeoffs between the benefits of milk production and consumption and AFM_1_ risk. Ethiopia has recently adopted a strict standard for AFM_1_ in milk, 0.5 µg/L (Ethiopian Standards Agency CES-278), which is often exceeded in raw milk samples from Ethiopia as shown by mean AFM_1_ levels ranging between 0.41 and 0.69 µg/L with a range of 0.028–4.96 µg/L.^14^ The action level for AFM_1_ in milk in the USA is the same, at 0.5 µg/L^15^; while the European Union standard is 0.05 µg/L.^16^ The recent lack of evidence linking AFM_1_ to cancer has led to the question of whether the standards set are reasonable.^12^ Moreover, dairy markets are important in Ethiopian livelihoods, particularly in rural areas where dairy is an important source of supplemental income.^17^ If excessively strict AFM_1_ standards are enforced in Ethiopian dairy markets, it could result in both economic losses from discarded milk, and nutritional losses due to negative public perception against milk consumption.^12 18^

To assess the relationship between AFM_1_ exposure and growth outcomes and the potential benefits and risks of AFM_1_ in milk in Ethiopia, we use a prospective longitudinal cohort design. Here, we describe the objectives, methods and expected outcomes of this study.

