### Data analysis

#### Empirical approach

Descriptive analysis will focus on computing frequencies and percentages for categorical variables and summary statistics (like means, medians SD, IQR) for summarising continuous variables. To determine the association between dairy consumption and growth outcomes in children 6–18 months of age at the baseline, we will specify a least squares regression model as:

(1)
$$Y_{iv}=\alpha +\beta_{M}M_{iv}+X_{iv}^{\prime }\delta +\varepsilon_{iv}$$

where 
$Y_{iv}$
 is the anthropometric outcome for a child *i* residing in enumeration area *v* measured at various time points. Variable 
$M_{iv}$
 measures the child’s milk intake at various time points. The regression controls for child, parent and household characteristics that are captured in vector 
$X_{iv}$
. These control variables are observable characteristics that are likely to be correlated both with a child’s milk intake and his/her growth outcomes. The terms 
α
 and 
$\varepsilon_{iv}$
 in equation (1) represent the intercept and error term, respectively. The coefficient 
$\beta_{M}$
 quantifies the conditional association between a child’s milk intake and subsequent growth outcome, measured either as HAZ at the end line or as change in HAZ between the baseline and end-line surveys. Considering previous evidence from Ethiopia and elsewhere, we expect 
$\beta_{M}$
 >0.

To determine the association between AFM_1_ levels in milk and nutrient density in milk, we will conduct a univariate analysis on each of the macronutrients and micronutrients and then carryout bivariate tests with AFM_1_ levels in the same samples and determine if and how they are associated with each other.

To determine the association between AFM_1_ exposure and growth outcomes in children 6–36 months of age who consume dairy, we will test whether the consumption of AFM_1_-contaminated milk is associated with lower HAZ (ie, more growth faltering) controlling for confounders and co-factors, including the amount of milk consumed and nutrient content and pathogens in the milk. We will append equation (1) with a variable capturing the child’s AFM_1_ exposure (variable 
$A_{iv}$
). In this model, we also control for the estimated macronutrient and micronutrient content and pathogens (vector 
$C_{iv}^{`}$
) in the milk sample collected at the baseline from the household in which the child resides. We will also control for the child’s maize consumption (vector 
$H_{iv}^{`}$

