), since maize is also likely to be contaminated by aflatoxins in the Ethiopian setting.^34–37^ The estimated model can be defined as:

(2)
$$Y_{iv}=\alpha +\beta_{M}M_{iv}+\beta_{A}A_{iv}+\beta_{C}C_{iv}^{\prime }+X_{iv}^{\prime }\delta +H_{iv}^{\prime }\vartheta +\varepsilon_{iv}.$$

We expect that 
$\beta_{A}$
 < 0.

To compare the health benefits versus risks of dairy consumption in child growth outcomes, we will use the regression estimates from equation (2) to conduct joint hypothesis tests for 
$\beta_{M}$
 and 
$\beta_{A}$
, where the null hypothesis is that both of these coefficients are zero, to inform benefit-risk tradeoff of dairy consumption in the context of AFM_1_.

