#### Estimation methods

The primary outcome variables in most of our statistical models will be continuous and will therefore typically be estimated using the Ordinary Least Squares method. As secondary outcomes, we will also examine dichotomous outcomes—such as stunting or wasting—as dependent variables, in which case we will use both linear probability models and Probit models to implement the regression analysis. Homoscedasticity in the residuals will be tested and if rejected, the SEs will be adjusted for heteroscedasticity following.^38^ All statistical analyses will be conducted using Stata, V.17 or higher.

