Despite these limitations, the results of our study will inform policy decisions on the appropriate AFM_1_ standards for commercial milk and dairy products, on measures to mitigate AFM_1_ risks and on improvement of knowledge of AFM_1_ risks among dairy consumers, producers, and other dairy value chain actors.

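### One AFM1 slope and a joint zero test cannot show whether growth differs across the 0.5 µg/L limit that the study intends to inform

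*Protocol article*

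**What the plan says.** **Model.** In Data analysis, Empirical approach, the article starts from a linear regression of the growth outcome on milk intake and covariates, and then states: "We will append equation (1) with a variable capturing" the child's AFM1 exposure. Equation (2) carries this as one variable, A_iv, with one coefficient, beta_A, which is expected to be negative. Under Estimation methods, models for continuous outcomes will "typically be estimated using the Ordinary Least Squares method".

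**Benefit-risk.** The comparison uses a joint test on beta_M (milk intake) and beta_A, "where the null hypothesis is that both of these coefficients are zero".

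**Scale.** The article does not say whether A_iv is a concentration, concentration multiplied by intake, or a logarithm of either.

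**Intended use.** The Introduction questions whether current limits are reasonable. It describes "a strict standard for AFM_1_ in milk, 0.5 µg/L" for Ethiopia and adds that "the European Union standard is 0.05 µg/L". The fourth objective is to develop recommendations on regulating AFM1. The Discussion speaks of setting standards at a level matched to the real risk and closes by saying that "the results of our study will inform policy decisions on the appropriate" AFM1 standards.

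**Expected exposure.** For Ethiopian raw milk the Introduction cites "mean AFM_1_ levels ranging between 0.41 and 0.69 µg/L with a range of 0.028–4.96 µg/L".

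**The concern.** A limit is a statement about a concentration: milk above it is rejected and milk below it is accepted. To inform its level, an analysis has to say something about growth on either side of it. Equation (2) fixes the shape of the relation in advance, and the joint test asks only whether both coefficients are zero. A significant negative beta_A would fit steady harm across the whole range, harm confined to milk above 0.5 µg/L, or harm only at the highest levels. These patterns have different implications for a standard.

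The article itself says that an over-strict limit leads to discarded milk and lost nutrition. A straight line that credits some harm to milk already under the limit could therefore push policy in the wrong direction. A second, conditional issue is that an untransformed and strongly skewed exposure would make beta_A depend heavily on its upper tail.

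**Working it through.** **1. What one slope can say.** The fitted HAZ difference between exposures a and b is beta_A × (b − a) on the raw scale, or beta_A × ln(b/a) on the log scale.

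- Raw: from 0.05 to 0.5 µg/L it is 0.45 × beta_A; from 0.5 to 0.95 it is again 0.45 × beta_A.
- Log: from 0.05 to 0.5 it is ln(10) × beta_A; from 0.5 to 5 it is again ln(10) × beta_A.

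On both scales the chosen scale, not the data, sets how the effect below the limit compares with the effect above it. If A_iv is concentration × intake, half the concentration at twice the intake gives the same A_iv, so the limit is not identifiable from A_iv at all. This step needs no distributional assumption.

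**2. What the joint test can say.** Rejecting beta_M = beta_A = 0 says that at least one coefficient is non-zero. It can reject through milk intake alone and carries no information about a level of AFM1.

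**3. Skew of the cited data (Introduction).** 4.96 / 0.028 = 177. The maximum is 4.96 / 0.69 = 7.2 to 4.96 / 0.41 = 12.1 times the cited means.

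**4. Leverage if A_iv is raw concentration.** Assumptions, not in the article:

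- lognormal concentrations, clipped to 0.028–4.96 µg/L
- mean 0.41, 0.55 or 0.69 µg/L
- log-SD = ln(177.1)/5, /6 or /7 = 5.18/5, 5.18/6 or 5.18/7 = 1.04, 0.86 or 0.74
- n = 1000 × 0.9 = 900, from the target sample and 10% attrition, counting every child as a milk consumer

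Share of the sum of squares of A_iv about its mean, over the nine combinations:

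| Most extreme samples | Raw scale | Log scale |
|---|---|---|
| 1% (9 of 900) | 28–41% | 7–8% |
| 5% (45 of 900) | 57–71% | 25–28% |

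A separate run with n = 720 gave 55–68% for the top 5% on the raw scale, so the result hardly depends on n.

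**5. Illustration of the shape problem.** Middle case: mean 0.55, log-SD 0.86, residual SD 1.56 (the article's HAZ SD), no covariates, n = 900, 500 runs (Monte Carlo error about 2 points). Neither true shape comes from the article.

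| Assumed truth | Power, raw linear | Power, log | Power, above-0.5 indicator |
|---|---|---|---|
| Step of −0.3 HAZ above 0.5 µg/L | 47% | 59% | 79% |
| Linear, −0.3 HAZ per µg/L | 89% | 76% | 55% |

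Under the step, the raw slope averages −0.18 per µg/L. It therefore implies −0.18 × 0.45 = −0.08 HAZ between 0.05 and 0.5 µg/L, where the assumed effect is zero. For scale, with about 37.5% of samples above 0.5, the unadjusted standard error of the above/below contrast is 1.56 × √(1/337.5 + 1/562.5) = 0.11, so this error is smaller than one standard error.

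**6. Can the data support the contrasts?** Over the nine combinations about 24–53% of samples exceed 0.5 µg/L, so that contrast is well populated. The share below 0.05 µg/L is Φ((ln 0.05 − mu)/s), with mu = ln(mean) − s²/2:

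- mean 0.41, s = 1.04: mu = −1.43, giving Φ(−1.51), about 6.5%
- mean 0.69, s = 0.74: mu = −0.64, giving Φ(−3.18), about 0.1%

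A statement at 0.05 µg/L would rest on few or almost no samples.

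**The case against.** **Detail left to a fuller document.** A journal article condenses its plan. Transformations, splines and influence checks commonly sit in an analysis plan that is not shown, and nothing here excludes them. This stands as regards their mere absence. It does not answer the mismatch: the article commits to an equation, an expected sign and a test built on its coefficients, and ties the results to the level of a standard.

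**The stated goal is association.** The Objectives section asks whether exposure is associated with impaired growth, which one slope suits. No section promises to find a threshold or to compare 0.05 with 0.5 µg/L, and the article disclaims causal inference. This stands, and is why the single-slope test should remain.

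**Leverage is not a defect in itself.** Wide exposure spread is information. If the truth is linear, the raw term is the most powerful of the three forms tried. This stands in full.

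**A stronger reading that a reader might infer:** that a handful of extreme samples will drive beta_A, so the planned estimate is unreliable and a log scale should replace it. The documents do not support this. A logged A_iv fits equation (2) as printed and would remove most of the leverage. The 177-fold range is milk concentration from cited Ethiopian samples, not exposure of the study children. The percentages depend on an assumed lognormal. A log term is also still one slope, so it would not address the limit either.

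**Conclusion.** The concern holds as a mismatch between the stated model and one of its stated uses. Equation (2) and the joint test can address whether AFM1 exposure is associated with HAZ. They cannot show whether that association differs below and above 0.5 µg/L, whichever scale A_iv takes. This part rests only on the algebra and the article's own text.

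The leverage figure is conditional. If A_iv is untransformed and distributed like the cited milk data, roughly 55–70% of the exposure sum of squares would sit in the top 5% of samples under a lognormal. It is a reason to state the scale and check influence, not evidence of bias. The power figures and the spurious −0.08 HAZ illustrate what an unmodelled step could do; neither truth is supported by the documents. The planned test of association is not invalidated. The change is worth making because it is cheap and bears directly on the policy question.

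**What to change.** Keep the single-slope model as the test of association, and state what A_iv is (concentration, or concentration × intake) and its scale. Add as pre-specified supporting analyses, with the same covariates:

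- (a) A contrast of HAZ for children whose milk AFM1 is above 0.5 µg/L versus at or below it.
- (b) A restricted cubic spline with 3 knots in milk AFM1, reporting with its confidence interval the fitted HAZ difference at 0.5 µg/L against a low reference percentile. The contrast alone would also be non-zero under a straight line; the spline shows the shape.
- (c) A log-scale refit or an influence check on beta_A.

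Limit statements about standards to concentrations that the data cover, and make no claim at 0.05 µg/L if few samples fall below it.

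**Cost.** A few lines of analysis on data already to be collected, and one or two extra degrees of freedom. A dichotomised contrast has less power than the linear term when the relation is truly linear (55% versus 89% in the illustration), so these analyses should support the linear test and not replace it.

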## Abstract

**Introduction:**

In Sidama, Ethiopia, animal-source foods can be difficult to access. Milk has important nutrients for child growth, but carries the risk of aflatoxin M_1_ (AFM_1_) contamination. AFM_1_ is a metabolite of the mycotoxin aflatoxin B_1_ (AFB_1_) in dairy feed; cows secrete AFM_1_ in milk when their feed contains AFB_1_ produced by *Aspergillus* fungi in maize, nuts and oilseeds. It is unknown whether AFM_1_ compromises child growth and health.

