**Methods and analysis:**

This protocol paper describes our study in Sidama to determine the impact of milk consumption and AFM_1_ on child growth in the first 18 months of life. We will collect baseline and end-line data on dairy production, socioeconomic and nutritional factors of 1000 dairy-owning households with children ages 6–18 months at baseline; and gather samples of milk and dairy feed and child anthropometrics. We will conduct phone interviews every 6 months to ascertain changes in practices or child health. Dairy feed will be tested for AFB_1_; milk for AFM_1_, pathogens and nutrients. Controlling for herd size, socioeconomic, nutritional and behavioural factors, we will determine the association between child anthropometrics and milk consumption, as well as AFM_1_ exposure. We will examine whether AFM_1_ exposure affects child growth in the first 18 months of life, and weigh the benefits and risks of milk consumption.

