## Introduction

Aflatoxins are secondary metabolites of the fungi *Asperfillus flavus* and *A. parasiticus*, which frequently infect food and feed crops such as maize, groundnuts, oilseeds and tree nuts.^1^ Aflatoxin B_1_ (AFB_1_) is the most toxic form of aflatoxin, and a potent liver carcinogen. Aflatoxin M_1_ (AFM_1_), a metabolite of AFB_1_, is excreted in milk when mammals consume feed contaminated with AFB_1_. Infants and young children can become exposed to AFM_1_ through dairy animal milk consumption. Although AFM_1_ is a far less potent carcinogen than AFB_1_, it may cause other health risks. Furthermore, knowledge of the tradeoff between the nutritional benefits of milk versus risks of AFM_1_ exposure in milk is currently sparse.

Globally, milk is a critically important animal source of food for infants and young children, providing a wide range of nutrients—protein, carbohydrates, fat, calcium, potassium and vitamin B_12_ among others—crucial for growth and development.^2–4^ Including milk in children’s diets is all the more important when access and affordability of other animal-sourced food such as meat and eggs are difficult.^5^ In addition, milk products are economically valuable; as the dairy value chain contributes substantially to livelihoods in semi-urban and rural areas worldwide.^6–8^

Conversely, milk can harbour multiple contaminants such as AFM_1_. AFB_1_, the parent compound of AFM_1_, may impair child growth^9^ through several pathways such as disruption of insulin-like growth factors,^10^ intestinal damage^11^ and immunosuppressive effects that increase infection susceptibility.^12 13^ Whether AFM_1_ could cause similar effects is unknown. This research study aims to fill this knowledge gap by examining the relationship between AFM_1_ exposure and growth outcomes in infants and young children in Ethiopia.

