### Control variables

Data on the control variables will be collected during the survey visits and will include characteristics that are likely to be correlated with child growth outcomes and child’s milk intake. This includes variables such child’s sex, age and diet, parent’s education, household wealth index, milk’s nutrient content, pathogens in milk and child’s maize consumption.

A questionnaire will collect information about child, parent and household characteristics. Information on children’s diet comes from the 24-hour recall survey. We will control for children’s diets by calculating caloric intake variables from eight food groups: (1) Breastmilk, (2) Grains, roots and tubers, (3) Pulses, nuts and seeds, (4) Dairy products, (5) Flesh foods (meats, fish, poultry, organ meats), (6) Eggs, (7) Vitamin-A rich fruits and vegetables and (8) other fruits and vegetables.^26^ Additionally, we will collect detailed data on the non-standard recipe’s ingredients for all mixed dishes that were prepared at home and use standard recipes from the National Food and Nutrition baseline survey dietary data set to assess the amount of food consumed.^27^ The dietary surveys will be administered outside of major Ethiopian Orthodox fasting periods during which dairy household availability and consumption may decline sharply.^28^

One potential source of measurement error in linking food consumption to child growth is within-person variability in consumption. Since linear growth in young children depends on long-term dietary quantity and quality, the 24-hour recall method is imperfect for capturing variability in diets over time.^29^ To address this, we will conduct interim phone surveys every 6 months to ask caregivers about the 24-hour milk consumption and weekly recall of the child’s diet diversity, and assess basic milk production. These higher frequency measurements will be used to assess seasonality, variability, and to adjust for consumption variability in our analysis.

A subsample of 500 livestock feed samples will be collected for testing AFB_1_. Detection of AFB_1_ in feed samples will be achieved using the Helica Low Matrix Aflatoxin B_1_ competitive ELISA kit, manufactured by Helica Biosystems, Santa Ana, California, USA, listed under Catalogue Number 981BAFL01LM-96 and using procedures outlined by them.^30^

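### Equation (2) adjusts for how much maize the child eats, not how contaminated it is, so beta_A can be biased negative if contamination of the child's maize and of the cow's feed is correlated

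*Protocol article*

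**What the plan says.** Protocol article, Data analysis, Empirical approach: equation (2) regresses the growth outcome on milk intake, AFM1 exposure (coefficient beta_A), milk nutrients and pathogens, household covariates and a vector H. On H the text says "We will also control for the child’s maize consumption", and gives as the reason "since maize is also likely to be contaminated by aflatoxins in the Ethiopian setting". The expected sign of beta_A is negative.

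Four other places bear on this:

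- Abstract, Introduction, on where AFM1 comes from: "cows secrete AFM_1_ in milk when their feed contains AFB_1_ produced by *Aspergillus* fungi in maize, nuts and oilseeds".
- Introduction: AFB1, "the parent compound of AFM_1_, may impair child growth".
- Control variables, on the rest of the child's diet: "We will control for children’s diets by calculating caloric intake variables from eight food groups".
- Abstract, Methods and analysis, on assays: "Dairy feed will be tested for AFB_1_; milk for AFM_1_, pathogens and nutrients". Control variables adds: "A subsample of 500 livestock feed samples will be collected for testing AFB_1". No assay of the child's maize or other food is listed, and no aflatoxin biomarker in the child.

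**The concern.** By the plan's own reasoning, the confounder is the child's aflatoxin dose from maize, which is amount multiplied by contamination. H and the food-group calories are both amounts, so contamination is left out.

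The plan also names maize as a source of AFB1 in cow feed. If a household's cow and child draw on the same store or local supply, a bad batch raises milk AFM1 and the child's direct AFB1 intake together. Holding the amount of maize fixed does not separate the two. Since AFB1 may impair growth, the leftover confounding pushes beta_A down, which is the direction the plan expects. A spurious result would therefore look like confirmation.

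The Discussion would use the result to judge whether strict AFM1 standards for milk are justified, and it considers a reading in which AFM1 itself causes poor growth. An association that really came from contaminated maize would then count as evidence on milk.

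**Working it through.** The plan states no figure for this point, so there is none to reproduce. The check asks what equation (2) returns when the true beta_A is 0.

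**Inputs from the protocol article.** SD of HAZ 1.56; significance level 5% (taken as two-sided, which the text does not state); about 1000 children less 10% attrition, so n = 900. Equation (2) concerns children who consume dairy. Their share is not given, so n = 500 is used as a lower case.

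**Assumptions, none given in the documents.** Geometric SD of maize amount 2 (log-SD 0.69); log-SD of maize contamination s = 1.0 to 1.5; share of children eating maize p = 0.6 to 0.8; AFB1 effect b = -0.2 to -0.3 HAZ per SD of log dose; correlation r between log milk AFM1 and log contamination of the child's maize.

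**Step 1: how much of the dose does amount capture?** The share of variance in log dose due to amount is 0.69² / (0.69² + s²):

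- s = 1.0: 0.476 / 1.476 = 0.32
- s = 1.2: 0.476 / 1.916 = 0.25
- s = 1.5: 0.476 / 2.726 = 0.17

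Amount accounts for about 17-32% of it; the rest is contamination.

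**Step 2: bias in beta_A.** With amount held fixed, one SD of log AFM1 goes with r SDs of log contamination. In SDs of log dose that is r × k, where k = s / √(0.69² + s²). If AFM1 is unrelated to maize amount and to who eats maize, bias ≈ p × b × k × r. For s = 1.2, k = 1.2 / 1.384 = 0.867.

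- r = 0: bias 0.
- r = 0.2, b = -0.2: 0.6 × (-0.2) × 0.867 × 0.2 = -0.021, and -0.028 at p = 0.8.
- r = 0.4, b = -0.2, p = 0.6: -0.042.
- r = 0.6, b = -0.3, p = 0.8: -0.125.

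Simulations of equation (2) by least squares gave -0.02 to -0.04 in the second case and -0.04 to -0.12 across correlations of 0.4 to 0.6.

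**Step 3: false rejection.** The SE is about 1.56/√n, which is 0.070 at n = 500 and 0.052 at n = 900. With z = |bias|/SE, rejection is Φ(z - 1.96) + Φ(-z - 1.96).

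| Setting | n = 500, formula | n = 900, formula | Simulated |
|---|---|---|---|
| r = 0.2, b = -0.2 | 6-7% | 7-8% | mostly 3-12% |
| r = 0.4, b = -0.2, p = 0.6 | 9% | 13% | lower end: about 9% and 13% |
| r = 0.6, b = -0.3, p = 0.8 | 43% | 67% | upper end: about 40% and 60% |

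The formula runs a little above the simulations at the top end.

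**Step 4: is the missing term the cause?** In a second simulation, effects were set per SD of HAZ (-0.1 to -0.3 SD, so -0.16 to -0.47 HAZ) and are therefore larger. At n = 900 and a maize-feed correlation of 0.3, the bias was -0.05 to -0.14 HAZ and rejection 14% to 69%. Once the child's own AFB1 intake was added to the model, mean beta_A lay within 0.004 SD of zero in every cell and rejection was 3.9% to 6.7%.

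**Step 5: would a product term repair it?** One could add maize intake × milk AFM1 and read beta_A at zero maize. With perfect recall at the strongest setting, this still left a bias of -0.05 to -0.08 and 10-20% rejection. Then suppose 5% of children truly eat no maize and an eater has a 50-70% chance of reporting maize in a one-day recall (r = 0.5, b = -0.3, n = 900). Equation (2) gave -0.12, the product-term estimate at zero maize also about -0.12 with 40-52% rejection, and a no-maize subgroup defined by that single recall -0.11 to -0.12 with 24-40% rejection.

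**The case against.** The key link is assumed. No section says that cow and child share maize. The Abstract names maize, nuts and oilseeds as general background and does not describe feed in these households. The target households are urban or peri-urban, the districts were chosen partly because market access to feed varies, and bought or mixed feed would weaken a shared-store link. Herd size, with which feed type varied, is the sampling stratum and is controlled according to the Abstract. The formative results that might settle the matter are reported elsewhere. At weak correlations the distortion is close to nil. The article also disclaims causal inference and says that only observable confounders are controlled, so this could be called ordinary residual confounding.

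Much of this stands. A reader might infer that equation (2) will produce a false AFM1 effect, or that the false-positive rate is 60%. The documents do not support either: they give neither the correlation nor the size of any AFB1 effect, and the high rates belong to one part of an unknown range.

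Two things remain. The causal disclaimer is general, and the listed limitations do not mention the child's own dietary AFB1, while the Discussion would still carry the coefficient into policy on AFM1. And the plan names this confounder, then fixes a term that does not measure it.

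**Conclusion.** The point holds in conditional form. Equation (2) controls the amount of maize and leaves its contamination uncontrolled. Beta_A is biased negative with no AFM1 effect if two conditions are met: contamination of the child's maize and of the cow's feed is positively correlated within households, and dietary AFB1 lowers HAZ. The article treats the second as possible and is silent on the first.

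Under the stated assumptions the size runs from nil at zero correlation, through a small distortion at 0.2, to one that could mislead at 0.4 to 0.6. Where this study lies on that range cannot be told from the documents. The problem is worth fixing because the bias has the expected sign and part of the remedy is cheap.

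**What to change.** - Keep equation (2) as the main model.
- Add one survey item: do the child's maize and the maize in the cow's feed come from the same store or seller? Report beta_A separately for shared-source and separate-source households.
- As a further sensitivity analysis, report beta_A among children with no maize in any available recall or diet-diversity report, not only in the single baseline 24-hour recall. The article describes the diet-diversity reports by food group, so they help only if maize is recorded separately from other grains.
- State in the limitations that maize quantity does not capture maize contamination. Do not describe beta_A as AFM1-specific if it is confined to shared-source or maize-eating children.
- Do not use a maize × AFM1 product term read at zero maize, or a maize × feed AFB1 term, as a pass/fail test. With one-day recall the first can leave most of the bias in place. In the second, feed AFB1 is the direct cause of milk AFM1, so adjusting for it may remove real signal, and only 500 feed samples are tested.

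The cost is one survey item and no new samples or assays. The Study timeline ends data collection in August 2025, so the item needs a remaining contact; the limitation statement does not, nor does the no-maize analysis where maize is already recorded. Subgroup estimates will be less precise, so they sit beside the main estimate and do not replace it. Households with separate stores may still share a local supply, so the split reduces the ambiguity without removing it.

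### Maize is the only diet term in equation (2) specified as an aflatoxin control; nuts, oilseeds and breast milk enter only as calories, and no diet term carries aflatoxin content

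*Protocol article*

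**What the plan says.** Under Empirical approach, equation (2) extends equation (1) with A (the child's AFM1 exposure), C (nutrients and pathogens in the household's milk sample) and H (the child's maize consumption). The reason given for H is "since maize is also likely to be contaminated by aflatoxins in the Ethiopian setting". No other diet term is justified in that way.

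Equation (2) also keeps X from equation (1): "The regression controls for child, parent and household characteristics that are captured in vector" X. The Control variables section lists the child's diet among the controls, and it is built by "calculating caloric intake variables from eight food groups: (1) Breastmilk, (2) Grains, roots and tubers, (3) Pulses, nuts and seeds", with five further groups after these.

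The Introduction describes the fungi as ones "which frequently infect food and feed crops such as maize, groundnuts, oilseeds and tree nuts". It says that AFB1, "the parent compound of AFM_1_, may impair child growth", and that AFM1 "is excreted in milk when mammals consume feed contaminated with AFB_1".

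On measurement, the Control variables section says: "A subsample of 500 livestock feed samples will be collected for testing AFB_1". AFM1 is assayed in the milk samples collected at the baseline and end-line visits. No assay of the child's food, of breast milk or of a child biomarker is described.

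**The concern.** H is there to separate AFM1 in cow's milk from aflatoxin that reaches the child by other routes. On the protocol's own premises, nuts and oilseeds are the same kind of route as maize. If children in households with more AFM1 in their cow's milk also take in more AFB1 from these foods, and AFB1 impairs growth, part of that effect is attributed to beta_A. With positively correlated sources the bias is negative, which is the direction the protocol expects for beta_A.

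Breast milk raises a related question of definition. If it carries AFM1, a variable built from the household's milk sample is not the child's whole AFM1 exposure, and the shortfall differs between breastfed and other children.

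This matters because beta_A is the coefficient from which the benefit-risk comparison and the advice on AFM1 standards are to be drawn.

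**Working it through.** **1. What each source gets in equation (2)**

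| Source | Named in the Introduction as an aflatoxin route | Calorie term (through X) | Own term as aflatoxin control |
|---|---|---|---|
| Maize | yes | yes, within grains, roots and tubers | yes (H) |
| Groundnuts, tree nuts, oilseeds | yes | yes, pooled with pulses | no |
| Breast milk | only by inference from mammals | yes | no |

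Maize is a grain, so it already falls in a calorie group. Its separate term shows that the authors did not regard a pooled group as enough for aflatoxin. The same reasoning applies to nuts and seeds, whose calorie coefficient is shared with pulses.

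**2. What an intake term can remove**

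All inputs in steps 2 to 4 are assumptions. The documents give neither dose effects nor correlations. True beta_A is set to zero.

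Let one omitted source have log dose d = (0.5q + c)/√1.25, where q is the amount eaten and c the contamination level. Let its effect be −0.10 outcome SD per SD of dose, and let the amount correlate r with cow-milk AFM1.

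- Bias without an amount term = −0.10 × 0.5 × r/√1.25 = −0.045r. At r = −0.4 this is +0.018.
- With the amount in the model, simulation gives 0.000.

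A separate intake term therefore removes confounding that runs through amounts.

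**3. What an intake term cannot remove**

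Now let the contamination level of each of three sources (maize, nuts, breast milk) correlate rho with cow-milk AFM1, each with an effect of −0.10. The expected spurious slope is about 3 × (−0.10) × rho. The table gives the simulated spurious beta_A per SD of AFM1.

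| rho | Maize amount only | Maize, nut and breast-milk amounts | Actual doses |
|---|---|---|---|
| 0 | 0.003 | 0.003 | 0.003 |
| 0.2 | −0.065 | −0.064 | −0.003 |
| 0.4 | −0.121 | −0.121 | −0.001 |
| 0.6 | −0.180 | −0.180 | 0.000 |

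Adding amounts changes nothing on this route, and the limit applies to the maize term too. Only measured doses would remove it.

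**4. Scale against sampling error**

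Take one omitted dose with effect −0.10 and residual correlation 0.2 to 0.4 with A. The bias is −0.02 to −0.04. With 1000 × 0.9 = 900 children, the smallest plausible SE is 1/√900 = 0.033, so the bias is 0.6 to 1.2 SE. A two-sided 5% test would then reject a true null in 9.2% to 22.4% of studies. The real SE will be larger, because A is likely to correlate with milk intake M and the model covers only milk-consuming children. The figures in SE units are therefore upper values for these inputs.

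**5. Breast milk as a share of AFM1**

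Assume 500 mL/day of breast milk at 0.01 to 0.05 µg/L (5 to 25 ng/day) and 200 mL/day of cow's milk. At the Ethiopian means cited in the Introduction, 0.41 to 0.69 µg/L, cow's milk supplies 82 to 138 ng/day. The breast-milk share runs from 5/(5 + 138) = 3.5% to 25/(25 + 82) = 23%.

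**The case against.** **Nuts and breast milk are already in the model.** This stands. Their calories are planned diet controls, and X is carried into equation (2). A reader might infer that the model adjusts for other intake through maize alone, and the documents do not support that. The defect is narrower: those terms are not specified as aflatoxin controls, and nuts are merged with pulses.

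**More intake terms do not cure shared contamination.** This also stands, as step 3 shows. The extra terms are worth having for the amount route only. A one-day recall measures that route with error, as the protocol itself acknowledges for diet.

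**Human milk is never named as an AFM1 source.** Correct. The Introduction speaks of mammals consuming feed, and the exposure it then describes is dairy-animal milk. A reader might infer that breast milk supplies most of a child's AFM1. With the intakes assumed in step 5, the share reaches 33% to 71% only if cow's milk is put at 0.05 µg/L (10 ng/day), roughly a tenth of the means the protocol cites.

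**Shared household crops are assumed.** The protocol says that these crops serve as food and feed, but it does not say that one household's cow, child and mother eat from the same stock. It also stresses variation in market access to feed. The correlation is plausible but not documented.

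**The limits are disclosed.** The protocol disclaims causal inference and claims control of observable confounders only. That covers contamination levels. It does not cover nut and oilseed intake, which the planned recall can observe. The Discussion also foresees policy consequences if AFM1 is found to cause poor growth.

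**Conclusion.** The point holds in a limited form. Equation (2) gives maize its own aflatoxin term but leaves nuts and oilseeds, which the protocol names alongside it, in a calorie group shared with pulses. This is an inconsistency within the stated model. Separately, every dietary control is an amount and none is an aflatoxin dose, so beta_A can still reflect AFB1 in food where contamination levels move together.

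No numerical bias can be claimed. The illustrations depend on assumed effects and correlations, and they give zero when contamination levels and amounts are unrelated to cow-milk AFM1. The breast-milk part rests on an inference and justifies a clearer definition of A and a sensitivity analysis, but no stronger claim.

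**What to change.** - Extend H to separate terms for the child's intake of maize, groundnuts and other nuts, and oilseeds, all from the same 24-hour recall. Keep pulses as their own calorie group.
- Add breastfeeding status at baseline as a covariate, and report beta_A by breastfeeding status as a sensitivity analysis.
- Define A as AFM1 from the household's cow's milk.
- State that the diet terms adjust for amounts eaten and not for aflatoxin content, that confounding through shared contamination levels remains (in maize as well), and that beta_A is to be read with that limit.

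The change is to analysis and wording. Foods are covered by the planned recall, which also collects ingredients of non-standard home-prepared dishes, and breast milk is already one of its food groups. The cost is a few degrees of freedom and wider intervals in the breastfeeding subgroups.
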